## Abstract

**Background:**

Proximal femoral fractures are amongst the most devastating consequences of osteoporosis and injurious accidental falls with 25–35% of patients dying in the first year post-fracture. Effective rehabilitation strategies are evolving however, despite established associations between nutrition, mobility, strength and strength-related functional outcomes; there has been only one small study with older adults immediately following fragility fracture where a combination of both exercise and nutrition have been provided. The aim of the INTERACTIVE trial is to establish whether a six month, individualised exercise and nutrition program commencing within fourteen days of surgery for proximal femur fracture, results in clinically and statistically significant improvements in physical function, body composition and quality of life at an acceptable level of cost and resource use and without increasing the burden of caregivers.

**Methods and Design:**

This randomised controlled trial will be performed across two sites, a 500 bed acute hospital in Adelaide, South Australia and a 250 bed acute hospital in Sydney, New South Wales. Four hundred and sixty community-dwelling older adults aged > 70 will be recruited after suffering a proximal femoral fracture and followed into the community over a 12-month period. Participants allocated to the intervention group will receive a six month individualised care plan combining resistance training and nutrition therapy commencing within 14 days post-surgery. Outcomes will be assessed by an individual masked to treatment allocation at six and 12 months. To determine differences between the groups at the primary end-point (six months), ANCOVA or logistic regression will be used with models adjusted according to potential confounders.

**Discussion:**

The INTERACTIVE trial is among the first to combine nutrition and exercise therapy as an early intervention to address the serious consequence of rapid deconditioning and weight loss and subsequent ability to regain pre-morbid function in older patients post proximal femoral fracture. The results of this trial will guide the development of more effective rehabilitation programs, which may ultimately lead to reduced health care costs, and improvements in mobility, independence and quality of life for proximal femoral fracture sufferers.

**Trial registration:**

Australian Clinical Trials Registry: ACTRN12607000017426.

## Background

Proximal femoral fracture (PFF) is amongst the most devastating consequences of osteoporosis and injurious accidental falls with 25–35% of patients dying in the first year post-fracture [1,2], only 40% returning to pre-fracture level of mobility [3], 15% failing to regain sufficient independence to remain in their own home [4] and annual expenditure for fractures in the United States alone exceeding $20 billion [5]. With the world-wide number of hip fractures projected to approximately double to 2.6 million by the year 2025, and 4.5 million by the year 2050, there is an urgent need to develop preventive strategies [6].

For older people who sustain PFF, rapid deconditioning, loss of muscle strength and weight loss often develop. Causes for this may include inadequate dietary intake, hypermetabolism, and a decline in skeletal muscle mass as a result of a complex interaction between immobility, sarcopenia, wasting and possibly cachexia [7,8]. Muscle weakness can lead to impaired balance and slowed gait speed and it is likely that this rapid deconditioning is partly responsible for the hospital readmissions, repeat injurious falls and loss of independence associated with PFF in older people [9-12].

Exercise programs with community-dwelling, medically stable older adults have been extensively evaluated, the findings suggesting significant reductions in falls [13-15], injuries [13,14], activity restrictions [16] and improvements in balance [17,18]. However, only a small number of exercise studies have been undertaken beginning in the early recovery phase after PFF. All have evaluated the effect of a strengthening program incorporating progressive resistance exercise and, while the findings of some studies appear to be positive in terms of improved strength, gait speed, balance and quality of life (QOL) [19-24], others have found no effect on physical performance and an increased risk of subsequent injury [25]. However, many of these studies were undertaken on samples combining PFF patients with other diagnostic groups (e.g. frail, elective, orthopaedic) and hence the impact of an exercise program for PFF patients alone is uncertain. Also, many studies have commenced after rehabilitation when it is likely that there has already been rapid deconditioning and significant decline in skeletal muscle mass and strength.

The quality of evidence supporting nutritional interventions following PFF is limited and inconsistent [26]. One of the main limitations of studies evaluating the effect of nutrition support following PFF is the lack of attention to the provision of an adequate amount of energy and protein to address the deficits associated with pre-existing undernutrition [26], injury and surgical stress [27] and inadequate dietary intakes during recovery [7,8]. Indeed, most nutrition support studies prescribe a standard volume of oral supplement based on a convenient number of tins rather than individual needs [26] and there are no studies that approximate usual clinical care by also including individual goal setting, menu modification and counselling.

Despite established associations and potential interactions between nutrition, mobility, strength and strength-related functional outcomes, there has been only one small study (n = 100) amongst older adults immediately following lower limb fragility fracture where a combination of both exercise and nutrition have been provided [28]. In this study interventions commenced seven days following injury and consisted of either an individually prescribed multi-nutrient energy dense oral supplement for six weeks, tri-weekly resistance training for 12 weeks, combined treatment or attention control. The findings of this small study highlighted for the first time that nutritional management with a concurrent exercise program post lower limb fragility fracture may be able to prevent significant weight loss. Despite clinically significant weight loss across all treatment groups, this study identified that it is possible to achieve weight maintenance if strategies are implemented to ensure the nutrition supplementation prescription is adequate to achieve energy balance and levels of adherence are high. It also suggested that a comprehensive approach to nutrition support, rather than oral supplements alone, is likely to be required to improve nutritional status and hence impact positively on functional outcomes or quality of life (QOL).

The aim of this randomised controlled trial (RCT) is to implement a six month, individualised exercise and nutrition program commencing within 14 days of surgery for PFF, that will result in clinically and statistically significant improvements in terms of physical function, body composition and QOL at an acceptable level of cost and resource use and without increasing the burden of caregivers. Comparisons will be drawn with the attention control group.

## Methods and Design

### Design overview

A two-site RCT with masked outcome assessment and 12 month follow up of 460 community-dwelling older adults post PFF. Participants will be randomly allocated to: a) six month individualised exercise and nutrition program (intervention group) or b) attention control (control group). An overview of the recruitment method, randomisation process and follow-up procedures is provided in Figure 1.

**Figure 1 F1:**
[figure not shown]
Study design and assessment points.

### Recruitment and eligibility

Participants will be recruited from two acute care settings: Flinders Medical Centre (Adelaide), and Hornsby Ku-ring-gai Hospital (Sydney). Eligible individuals will be all those admitted with a diagnosis of PFF confirmed by radiology report, aged 70 years and over and residing in the community, within existing local service boundaries.

Screening will be carried out for all individuals who meet these inclusion criteria by project personnel in consultation with members of the orthogeriatric team. Potential participants will need to achieve a mini-mental score (MMSE) > or = 18/30, as it is thought that participants with severe cognitive impairment [29] will be unable to independently follow therapeutic advice and have difficulty in verification of QOL and other outcomes. If a score of = 18/30 or above is not achieved on the first attempt following surgery and post operative delirium is suspected then the MMSE will be repeated at a later date (but still within 14 days of injury) to see if a MMSE score of = 18/30 or above can be achieved. Participants must also have a body mass index (BMI) between 18.5 kg/m^2 ^and 35 kg/m^2^. A BMI less than 18.5 kg/m^2 ^is considered to be underweight [30] and ethically these patients should receive nutrition support as standard care. Patients with a BMI >35 kg/m^2 ^(morbidly obese) [30] will be excluded from participating in the study as there is currently no evidence that the same level of decline in body weight exists for these patients and these patients are likely to have multiple medical co-morbidities increasing the complexity of the study intervention.

Exclusion criteria include a pathological fracture or malignancy; those residing in residential care, non-English speaking, limited to stand transfers only post surgery or non ambulatory pre fracture, unable to give informed consent or not deemed to be medically stable within fourteen days post surgery. All those individuals who meet the inclusion and exclusion criteria will be invited to participate. When study personnel are satisfied that an individual understands the study information and implications of their involvement, written informed consent will be obtained prior to commencement of baseline measures and randomisation. In the situation where it is felt that a participant does not have the capacity to give informed consent (i.e. post-operative delirium or mild cognitive impairment) third party consent will be obtained from a close relative or immediate caregiver.

The Flinders Clinical Research Ethics Committee reviewed and approved the study protocol – Research Application 110/067.

### Measurements and Procedures

#### Baseline, six and 12 month follow-up

Project personnel will assess the selected outcome measures at baseline (prior to randomisation) whilst an individual masked to treatment allocation will assess outcomes at six and 12 months. Testing will coincide with maximum effect of each participant's analgesic regime. Outcome measures have been selected based on suitability for older adults following PFF, strength of the evidence to support validity and reliability, significance to rehabilitation and previous use in the literature.

The baseline assessment protocol entails a detailed multi-dimensional health assessment by means of:

**a) Physical Function, Strength and Balance: **Physical autonomy will be measured using a physical and instrumental ADL scale [31]. A subjective rating of pain for three separate activities of daily living (ADL) will be established prior to physical testing, which include knee extensor strength using a Nicholas Manual Muscle Tester (NMMT) [32] and a 30 second chair stand test [33], gait speed via a 3 m Walk Test [34], balance on the modified Berg Balance Scale (MoBerg) [35] and grip strength using a hand held dynamometer [36].

**b) Body Composition and Nutrition Measures: **Percent weight change will be assessed using calibrated scales. Body composition (fat free mass) will be measured at baseline, six and 12 months using dual-energy x-ray absorptiometry (DEXA: Lunar Prodigy, GE Healthcare, UK). Lumbar spine and proximal femur DEXA scans will also be performed to assess changes in bone mineral density. Triceps skinfold measures and mid upper arm circumference (MUAC) will also be measured to determine corrected arm muscle area (CAMA) [37]. Appetite will be assessed using the Council on Nutrition Appetite Questionnaire (CNAQ) [38] and 24 hour dietary recall recorded using a standardised protocol [39].

**c) Questionnaires: **Assessment of Quality of Life Instrument (AQoL) [40], a four item summary scale created from the CES-D [41] to determine positive affect and a self rated health survey. In addition caregivers will also complete a caregiver burden and strain index [42,43].

#### Additional Information

Monitoring of participants for six months via weekly home visits will allow for an account of any change in accommodation, falls and injuries and any change in health status. At 12 months participants will be contacted via telephone to organise the follow-up assessment. If there is no response then project personnel will contact the next of kin.

#### Economic evaluation

Within study analysis will be undertaken based on observed effects and resource use, including hospital inpatient admission and length of stay from medical records, PBS and MBS use from the Health Insurance Commission (Medicare and Pharmaceutical Benefits), as well as direct costs of the proposed intervention (staff, travel, equipment). Use of community services will also be estimated based on a weekly survey administered to all participants.

### Randomisation and blinding

Participants will be randomly assigned to either the combined nutrition and exercise therapy group or the attention control group following completion of all baseline measures. Group allocation will be managed externally by the Pharmacy Department at the Repatriation General Hospital. Therapists and participants will be aware of treatment allocation however staff performing the outcome assessments and the data analysis will remain unaware of allocation.

### Intervention

Participants allocated to the intervention group will receive a well-integrated, coordinated, individualised care plan combining resistance training and nutrition therapy commencing between day seven to 14 post-surgery and continued over a six month period. Therapists administering the intervention across the two sites will be trained in the established protocols and fidelity to protocols will be addressed through random checks of therapy sessions and fortnightly project staff meetings.

The Otago exercise program [44] has been chosen for its ease of implementation, affordability and effectiveness in terms of falls reduction in older adults [13,14,45]. The program will be supervised until the physiotherapist feels confident that the participant is capable of carrying out the strength, balance and walking program independently and safely. At this point, they will be encouraged to complete the exercise program at a minimum of tri-weekly, along with tri-weekly walking outside of the home with the physiotherapist continuing to visit on a fortnightly basis for the purpose of encouragement, review and upgrading the program. This will all be recorded in an exercise diary maintained by patients and carers to monitor adherence.

As a basis for developing a nutrition program that will achieve energy balance (and hence prevent clinically significant weight loss), the resting energy expenditure (REE) of each participant will be measured using indirect calorimetry. Achieving the shortfall between estimated dietary intake (specifically energy and protein) and measured or recommended requirements, whilst considering risk factors threatening nutritional well-being, will become the focus of the nutrition care plan. Strategies for achieving energy and nutrient requirements will include counselling with attention to timing, size and frequency of meals, recommendations of nutrient dense foods, provision of recipes and referral to community meal programs and providers and supplementation with commercial liquid diets, protein supplements or multi-vitamins where deemed necessary by a dietitian. Intake of any prescribed supplements will be recorded by nursing staff while in hospital, and by the patient or caregiver once discharged home. Dietary intake and requirements will be reviewed on a fortnightly basis by a dietitian and modified as required.

Participants allocated to the attention control group will continue therapy as prescribed during hospital admission (acute and rehabilitation) according to current practice. Social visits of equivalent duration will occur to match the active intervention group. The project physiotherapist and dietitian will provide participants with generic nutrition, exercise and falls information in line with Government recommendations to provide some relevant topics for discussion, this information will also be given to the intervention group.

### Sample Size Considerations

Gait speed at six months was chosen as the primary outcome because safe, independent walking is a high priority amongst patients participating in rehabilitation, and gait speed is often recommended as a measure of status and outcome [46,47]. Using gait speed data collected from a recent study undertaken at the Adelaide site (n = 100) [28] it was calculated that a sample size of 176 participants per group will achieve a statistically and clinically significant 20% difference between the two groups (power 80%, alpha = 0.05). To allow for deaths and withdrawals (30%), 460 participants will be recruited, 230 per group.

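### The recruitment target does not cover the stated 30% loss: 230 per group leaves 161 evaluable, not 176, and about 76% power rather than 80%

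*Protocol article*

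**What the plan says.** The Sample Size Considerations section of the protocol article names gait speed at six months as the primary outcome. From data in an earlier 100-patient study at the Adelaide site, it concludes that a "sample size of 176 participants per group will achieve a statistically and clinically significant 20% difference", with the error rates given as "power 80%, alpha = 0.05". It then makes its allowance for loss: "To allow for deaths and withdrawals (30%), 460 participants will be recruited, 230 per group". The Abstract and the Design overview repeat the total of 460, the latter as "12 month follow up of 460 community-dwelling older adults post PFF". The inflation formula is not printed, and nothing elsewhere in the article changes the figure.

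**The concern.** The 176 is the number per group that must contribute a six-month gait speed for the power claim to hold. The 30% is attached to deaths and withdrawals, which happen among the people recruited. The number to recruit should therefore still leave 176 after 30% of it has been removed, and 230 does not.

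At stake is the stated power for the primary comparison. If loss reaches the level the plan itself assumes, the trial has less than 80% power for the difference it calls clinically significant. Readers would also take the sample to be protected against 30% loss when its real tolerance is lower.

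**Working it through.** **Inputs, all from Sample Size Considerations:** 176 evaluable per group; power 80%; alpha 0.05; 30% loss; 230 recruited per group (460 in total). The article does not say whether alpha is one- or two-sided. Two-sided is assumed here, and one-sided is checked below.

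**1. Reproducing the plan's target.**

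- Adding 30% of the evaluable number: 176 × 1.30 = 228.8, i.e. 229 per group or 458 in total. This is 460 after slight further rounding.
- Dividing by the retained fraction: 176 / (1 − 0.30) = 251.4, i.e. 252 per group or 504 in total. This does not give 460.

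Of the two usual routes, only the first gets near the stated figure. That it was the route used is an inference. The next step does not depend on it.

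**2. What 230 per group leaves.** 230 × (1 − 0.30) = 161 per group, 322 in total. The shortfall is 176 − 161 = 15 per group.

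**3. Loss that 230 can absorb.** 1 − 176/230 = 0.235, i.e. 23.5%.

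**4. Power at 161 per group.** The article gives no mean or standard deviation, so the 176 itself cannot be recomputed. They are not needed, because the plan's claim that 176 gives 80% power fixes the standardised difference:

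- d = (1.960 + 0.842) × √(2/176) = 0.2986 by the normal approximation. A two-sample t-test gives 0.2995.
- Power at 161 = Φ(0.2986 × √(161/2) − 1.960) = Φ(0.720) = 76.4%. The t-test also gives 76.4%.
- With one-sided alpha 0.05, d = 0.2651 and power is 76.8%.

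**5. Detectable difference at 161 per group with 80% power.** 20% × √(176/161) = 20.9%.

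**6. Power by actual loss from 230 per group** (normal approximation, two-sided):

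| Loss | Evaluable per group | Power |
|---|---|---|
| 20% | 184 | 81.7% |
| 23.5% | 176 | 80.0% |
| 25% | 172.5 | 79.2% |
| 30% | 161 | 76.4% |
| 35% | 149.5 | 73.3% |

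**The case against.** Five points can be made on the other side.

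- **The 30% may be a recruitment margin.** On this reading 30% was simply added to 176 and was never meant as a loss rate. But the sentence ties the percentage to deaths and withdrawals, so this is the less natural reading. Even then, the tolerated loss would be 23.5%, and the article should say so.
- **The horizon of the 30% is not stated.** Follow-up runs to 12 months, and the Background cites first-year mortality of 25–35%. If 30% is a 12-month figure, loss by six months could be below 23.5% and power would hold. This is possible, but the article does not say it, and the allowance directly follows a six-month calculation.
- **The planned ANCOVA may recover the power.** Gait speed is measured at baseline. A correlation of 0.3 with the six-month value would reduce the requirement to 176 × (1 − 0.3²) = 160.2 per group, which 161 meets. The algebra is right. However, Statistical Analysis speaks only of potential confounders, without naming baseline gait speed. No correlation is given, the sample-size text claims no such gain, and any gain already built into the 176 could not be counted again.
- **Intention to treat keeps everyone in the analysis.** It does not supply a gait speed for participants who have died, and the sample-size text itself treats deaths and withdrawals as losses to be made good.
- **The effect is small.** A loss of 3.6 points of power neither biases the treatment estimate nor inflates the type I error. This stands, and it argues for a light correction.

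**Conclusion.** The concern holds. The three printed figures (176 needed, 30% lost, 230 recruited) cannot all be true, because 230 × 0.70 = 161 whichever inflation formula was used. Under the plan's own loss assumption, power for the primary outcome is about 76%, not 80%, and 80% holds only up to 23.5% loss.

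This rests on taking 176 per group as giving exactly 80% power, on reading the 30% as loss of the six-month outcome, and on no gain from covariate adjustment. Whether alpha is one- or two-sided makes little difference. The error is modest in size and favourable in direction.

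**What to change.** Keep 460 and replace the allowance sentence with one that states what it delivers, for example: *With 460 participants randomised (230 per group) and 30% lost by six months, 161 per group remain, giving about 76% power for a 20% difference; 80% power is retained if loss does not exceed 23.5%.* If the 30% refers to 12 months, say so and give the loss expected at six months.

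A remark that adjustment restores the power should be added only if baseline gait speed is named as a covariate and the assumed correlation (about 0.3 or more) is stated as an assumption.

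The cost is one sentence, no extra participants, and a slightly less favourable power figure. If the sponsor instead wants 80% power at 30% loss without relying on adjustment, the target becomes 252 per group, 504 in total, which is 44 more than planned. The Time frame section says recruitment began in June 2007, so the restatement is the more practical choice.
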